### Statistical analysis

Our analysis of the primary outcome measure involves a comparison of the effectiveness of AOT + CAU versus CAU alone. Analysis will be conducted by intention to treat principles and the primary outcome measure will be percent days abstinent in the 90 days prior to 12 months follow up. AOT + CAU will be compared to CAU using analysis of covariance including stratification variables; SADQ and site as covariates. Multiple imputation and sensitivity analysis will be employed to assess the impact of missing data. Results will be presented as mean differences with associated 95% confidence intervals. Secondary analysis will address drinking and other outcomes at 6 and 12 months using appropriate modelling approaches and these will be adjusted for covariates; SADQ, site, age and gender. We will explore the association between engagement in treatment (measured by cumulative number of days in AOT and specialist alcohol treatment), readiness to change, and therapeutic alliance, and drinking outcomes using a linear regression adjusted for known confounders. As with most trials the analysis plan will be refined throughout the course of the study and the final analysis plan prepared and agreed by the research team and Trial Steering Committee.

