**Methods:**

One hundred and sixty ARFA patients will be recruited and following baseline assessment, randomly assigned to AOT plus care as usual (CAU) or CAU alone in equal numbers. Baseline assessment includes alcohol consumption and related problems, physical and mental health comorbidity and health and social care service use in the previous 6 months using standard validated tools, plus a measure of resource use. Follow-up assessments at 6 and 12 months after randomization includes the same tools as baseline plus standard measure of patient satisfaction. Outcomes for CAU + AOT and CAU at 6 and 12 months will be compared, controlling for pre-specified baseline measures. Primary outcome will be percentage of days abstinent at 12 months. Secondary outcomes include emergency department (ED) attendance, number and length of hospital admissions, alcohol consumption, alcohol-related problems, other health service use, mental and physical comorbidity 6 and 12 months post intervention. Health economic analysis will estimate the economic impact of AOT from health, social care and societal perspectives and explore cost-effectiveness in terms of quality adjusted life years and alcohol consumption at 12-month follow-up.

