### Baseline assessment

(i)Socio-demographic information: age, sex, ethnicity, marital status, living arrangement, children, living arrangements of children, education.(ii)Drinking in the previous 90 days – TLFB 90I [23]. The TLFB is a validated interview method to measure alcohol consumption in the previous 90 days and is the gold standard outcome measure in alcohol treatment research. Percentage days abstinent, units of alcohol per drinking day (1 UK unit = 8 g alcohol), time to first alcoholic drink, relapse to any drinking and relapse to heavy drinking (8+/6+ units for males/females on a single occasion) will be computed.(iii)History of drug use – TLFB.(iv)Alcohol related problems - Alcohol Problems Questionnaire (APQ) [24]. The APQ is a validated 46-item questionnaire assessing potential problems with psychological, physical, social, legal, employment, relationships and parenting that may be experienced due to alcohol.(v)Severity of alcohol dependence - Severity of Alcohol Dependence Questionnaire (SADQ) [25]. The SADQ is a validated 20-item self-complete questionnaire containing items representing five domains of the alcohol dependence syndrome: (i) physical withdrawal signs (ii) psychological withdrawal signs (iii) withdrawal relief drinking (iv) tolerance (v) reinstatement following a period of abstinence.(vi)Health related quality of life – EuroQol 5 dimensions 5 levels (EQ-5D-5 L) [26]. The EQ-5D-5 L consists of five dimensions (mobility, self-care, usual activities, pain/discomfort and anxiety/depression) scored on five levels (no problems, slight problems, moderate problems, severe problems and extreme problems). The EQ-5D-5 L is an extension of the original 3-level EQ-5D and has been shown to be valid [27].

This version of EuroQol measure of health-related quality of life capable of generating quality adjusted life years (QALYs) for use in economic evaluations.

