### Randomisation and blinding

Randomisation to one of the two treatment arms will take place after consent and baseline data have been collected, by a remote electronic allocation system. Once baseline data has been submitted on the electronic device by the researcher, the system will email the randomised allocation to a member of the clinical team. The researchers will be blind to the allocated intervention throughout the trial. The online system will be developed and maintained by Codeface Ltd. Randomisation will be stratified by site and severity of alcohol dependence (< = 30 and > 30), as measured by the Severity of Alcohol Dependence Questionnaire (SADQ).

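### The primary ANCOVA names SADQ and site but not baseline percent days abstinent, which the trial already collects: a free gain in precision is left unused

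*Protocol article*

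**What the plan says.** All references are to the protocol article.

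- **Primary outcome** (Statistical analysis): "the primary outcome measure will be percent days abstinent in the 90 days prior to 12 months follow up".
- **Primary model** (Statistical analysis): the arms are compared "using analysis of covariance including stratification variables; SADQ and site as covariates".
- **Secondary models** (Statistical analysis): "these will be adjusted for covariates; SADQ, site, age and gender". The Economic evaluation section uses SADQ and site again.
- **Baseline measurement** (Baseline assessment, item ii): "Drinking in the previous 90 days – TLFB 90I". The quantities to be derived from it begin with "Percentage days abstinent, units of alcohol per drinking day".
- **Timing** (Randomisation and blinding): "Randomisation to one of the two treatment arms will take place after consent and baseline data have been collected". Stratification is by site and by SADQ split at 30, not by drinking days.
- **Abstract, Methods**: outcomes will be compared "controlling for pre-specified baseline measures", without naming any measure.

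The Statistical analysis section adds that the plan will be refined and a final version agreed with the Trial Steering Committee. The Trial status section says that analysis is under way.

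**The concern.** The outcome is measured at baseline and at 12 months with the same instrument over the same length of window. Because baseline data are submitted before allocation is released, every randomised participant should have the baseline value. Yet none of the three covariate lists in the article contains it. The secondary list goes beyond the stratification factors, to age and gender, and still leaves it out.

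SADQ is an indirect stand-in. As the article describes it, it scores withdrawal, relief drinking, tolerance and reinstatement, not days abstinent.

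Two things are at stake. The first is precision, because outcome variance that baseline drinking could explain stays in the residual. The second is chance imbalance: the Discussion relies on randomisation to spread confounders equally, which is true in expectation but not in any one trial of this size. Any part of a baseline difference in drinking that SADQ and site do not capture passes into the treatment estimate.

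**Working it through.** **Inputs from the article (Sample size and power).** Effect size d = 0.4; two-sided α = 0.05; the stated β of 0.8 read as power 0.80; 64 analysed per arm; 20% loss; 80 recruited per arm.

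**Assumed input.** The correlation r between baseline and 12-month percent days abstinent is not given. The relevant quantity is the partial correlation given SADQ and site. The range taken is 0.3 to 0.5.

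**1. The plan's own figure.** n per arm = 2(1.960 + 0.842)² / d².
- At d = 0.4: 2 × 7.85 / 0.16 = 98.1, so 99 (about 100 by noncentral t), not 64.
- At d = 0.5: 2 × 7.85 / 0.25 = 62.8, so 63 (64 by noncentral t). The stated 64 matches 0.5.
- Inflation: 64 / (1 − 0.20) = 80, as stated.

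**2. Power at 64 per arm without the baseline covariate.** SE of the difference = √(2/64) = 0.177 SD. Power = Φ(0.4/0.177 − 1.960) = Φ(0.303) = 61.9% (61.2% by noncentral t).

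**3. Power with the baseline covariate.** The residual SD is multiplied by √(1 − r²).

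| Partial r | SE factor | Interval narrower by | Power, normal | Power, noncentral t |
|---|---|---|---|---|
| 0 | 1.000 | – | 61.9% | 61.2% |
| 0.3 | 0.954 | 5% | 66.0% | 65.3% |
| 0.5 | 0.866 | 13% | 74.3% | 73.7% |

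The r = 0 row lets SADQ and site explain nothing. If they explained 10% of the variance, power would be 66.5% without the baseline value, 70.6% with partial r = 0.3 and 78.6% with partial r = 0.5 (normal approximation). The gain is still about 4 and 12 points.

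**4. Would it restore 80% power?** With SADQ and site explaining nothing, that needs 98.1 × (1 − r²) = 64, so r = √(1 − 64/98.1) = 0.59, above the assumed range.

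**5. Chance imbalance in baseline drinking.** The baseline mean difference has standard deviation √(2/64) = 0.177 SD. P(|difference| > 0.2 SD) = 2[1 − Φ(0.2/0.177)] = 2[1 − Φ(1.131)] = 25.8%. This ignores stratification on SADQ, which lowers it to the extent that SADQ and drinking days are related.

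**6. Effect of such an imbalance.** Shift = r × 0.2 SD, which is 0.06 SD at r = 0.3 and 0.10 SD at r = 0.5. Against the 0.4 SD target these are 15% and 25%. The model's existing adjustment for SADQ would remove part of the shift.

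**The case against.** **The covariate list may not be closed.** The primary model is described with the word including, the abstract speaks of unnamed baseline measures, and a final plan was still to be agreed. So the article does not prove that the baseline value will be absent from the final analysis. That much stands. But none of these statements supplies the covariate. The only measures named are SADQ and site, with age and gender added for secondary outcomes. A named list that leaves out the baseline outcome is a stated choice that can be improved, not detail held over to the SAP.

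**The gain may be small.** No correlation is documented. Everyone must be alcohol dependent and a frequent attender, which could restrict the range of baseline drinking and lower r. SADQ may already carry part of the information. This stands, and it is why r is taken as partial. At 0.3 the gain is about 4 points of power.

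**Imbalance is not the expected case.** A reader might infer that a material imbalance is likely, or that the planned estimate is unadjusted. Neither is supported. The chance of exceeding 0.2 SD is about one in four, and the estimate is adjusted for SADQ and site.

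**Low power is a separate defect.** The shortfall comes from the sample-size statement. It makes lost precision more costly here, but it is not caused by the covariate list.

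**Not every secondary outcome has a baseline.** The therapeutic relationship scale is completed at 12 months, and patient satisfaction is added at follow-up. Time to first drink and relapse have no natural pre-treatment counterpart. A blanket rule would not work.

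**Conclusion.** The point holds as a free improvement. The named covariates leave out a baseline measure of the primary outcome that every randomised participant should already have.

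For a partial r of 0.3 to 0.5, using it would narrow the interval by about 5% to 13% and raise power at d = 0.4 with 64 per arm from about 61–62% to about 65–74%. It would also remove the part of a chance baseline imbalance that SADQ and site leave behind. These sizes rest on the assumed correlation and on a linear baseline-to-outcome relation.

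A reader might go further and infer that the planned comparison is biased or invalid. It is not: randomisation keeps it unbiased on average without this covariate. A reader might also infer that adding the covariate rescues the trial's power. Within the assumed range it does not, and the sample-size statement needs its own correction.

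**What to change.** Specify the primary model as: percent days abstinent at 12 months = arm + baseline percent days abstinent + SADQ + site.

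For secondary outcomes measured at baseline (for example units per drinking day, alcohol problems, quality of life and service use), add the outcome's own baseline value to SADQ, site, age and gender. Leave the list as it is for outcomes without one.

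Because analysis is already under way, record the change, with its date, before any unblinded comparison. If such a comparison has already been made, keep the stated model as primary and report the baseline-adjusted model as a sensitivity analysis.

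The cost is one degree of freedom per model, a short entry in the analysis plan and a documented decision made blind to allocation. No new data are needed.

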### Objectives

To conduct a randomised controlled trial of CAU + AOT versus CAU in a sample of alcohol related frequent attenders in five NHS trusts in South East London.To evaluate the effectiveness and cost-effectiveness of CAU + AOT versus CAU alone in ARFAs to acute and mental health inpatient care.To describe the characteristics and health and social care needs of ARFAs.To identify potential mechanisms of action of AOT and identify patient sub-groups for whom AOT is more effective.

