### Secondary hypotheses

CAU + AOT will be cost-effective compared with CAU alone at 12 months follow-up.CAU + AOT will reduce unplanned health care utilisation including admissions to Emergency Departments (ED) and acute and mental health inpatient care compared to CAU alone.CAU + AOT will increase engagement with specialist addiction and recovery services compared to CAU alone.Addiction treatment engagement, readiness to change and therapeutic alliance will moderate treatment effectiveness.

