### Follow up assessments

Six and twelve months after randomisation, all participants will be followed up (see Fig. 1). A research worker, blind to treatment allocation, will arrange a convenient time to meet with the participant. Baseline measures (items i-x above) will be repeated in addition to:
(xi)Therapeutic relationship – Scale to assess therapeutic relationship (STAR) [32] completed at 12 months follow-up. Therapeutic relationship (or alliance) has been found to predict clinical outcome across a range of mental disorders including alcohol dependence. This will be used as an additional process measure to assess the impact of therapeutic relationship on medication adherence and clinical outcome.

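### The moderation hypothesis is paired with a main-effect association regression, and two of its three factors arise after randomisation, so the analysis as written does not test it

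*Protocol article*

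**What the plan says.** Under Secondary hypotheses, the protocol article states: "Addiction treatment engagement, readiness to change and therapeutic alliance will moderate treatment effectiveness". Among the Objectives is the aim "To identify potential mechanisms of action of AOT and identify patient sub-groups for whom AOT is more effective".

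Under Statistical analysis, the same three factors appear once. The text reads "We will explore the association between engagement in treatment (measured by cumulative number of days in AOT and specialist alcohol treatment), readiness to change", then adds therapeutic alliance, and relates all three to "drinking outcomes using a linear regression adjusted for known confounders". No arm-by-factor term is named.

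On timing:

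- Under Follow up assessments, the alliance scale (STAR) is "completed at 12 months follow-up", and the text calls it a process measure.
- Readiness to change is item (viii) of the Baseline assessment. It is repeated at 6 and 12 months with the other baseline items.
- Under Control intervention, the assertive, regular contact that defines AOT is said not to be part of CAU.

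**The concern.** To say that a factor moderates treatment effectiveness is to say that the AOT-minus-CAU difference changes with the level of that factor. The parameter is an interaction between arm and a variable whose value does not depend on arm. The stated regression estimates a different parameter, the association between the factor and drinking.

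Two of the three factors are also unsuited to the role. Engagement days build up after randomisation and include AOT days, which controls do not receive by design. Alliance is recorded only at the visit that supplies the primary outcome. Patients who were going to drink less may stay in treatment longer and rate the relationship better, so a coefficient for either factor has several explanations.

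At stake is a listed secondary hypothesis. If the plan is followed as written, that hypothesis is left untested, and an association may be read as an answer to it.

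**Working it through.** **Inputs.** From Sample size and power: 64 analysed per arm, 128 in total, which is 80 recruited per arm × (1 − 0.20). I take that number as given. The document states no figure for the moderation analysis, so there is none to reproduce. Moderator splits, effect sizes and correlations below are my assumptions. Effects are in SD units of the outcome.

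**Step 1: what each model estimates.** Let the slope of drinking on a baseline factor be b₀ in CAU and b₁ in AOT. With 1:1 allocation and the same distribution of the factor in both arms:

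- coefficient in a model without interaction ≈ (b₀ + b₁)/2
- moderation = b₁ − b₀

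Either can be zero while the other is large. If b₀ = −0.25 and b₁ = +0.25, the first is 0 and the second is 0.5. If b₀ = b₁ = 0.25, the first is 0.25 and there is no moderation.

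**Step 2: the first case by simulation** (n = 128, average arm effect 0.4, standard normal factor, residual SD 1, 3,000 runs).

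| Test | Share with p < 0.05 |
|---|---|
| Main effect of the factor | 6% (about the nominal 5%) |
| Arm × factor interaction | 78% |

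**Step 3: engagement and alliance.** Suppose engagement has no causal effect, but an unmeasured prognostic factor correlates 0.5 with drinking and c with engagement. With arm in the model, the expected slope is 0.5 × c.

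| c | Expected slope | Simulated slope | Share with p < 0.05 |
|---|---|---|---|
| 0.5 | 0.25 | 0.25 | 82% |
| 0.3 | 0.15 | 0.15 | 39% |

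These values show the direction when prognosis is wholly unmeasured. Adjustment lowers them as far as the covariates capture prognosis. For 12-month STAR, adjustment for baseline confounders cannot settle whether alliance led to less drinking or the reverse.

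**Step 4: precision of a proper interaction test with 64 per arm.** For a binary baseline moderator with prevalence p:

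SE = √[2/(64p) + 2/(64(1 − p))]

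- p = 0.5: SE = √(4/32) = 0.354. Detectable difference at 80% power = (1.960 + 0.842) × 0.354 = 0.99 SD. Power is 20% at 0.4 SD, 29% at 0.5 SD and 62% at 0.8 SD.
- p = 0.3: SE = √(2/19.2 + 2/44.8) = 0.386. Detectable difference = 1.08 SD. Power is 18% at 0.4 SD.
- Continuous moderator: SE = √(4/128) = 0.177. Detectable change in effect = 2.802 × 0.177 = 0.50 SD per SD of the moderator.

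**The case against.** The best defence is that the analysis is modest. It only promises to explore associations, the document already calls STAR a process measure and speaks of mechanisms, and the final analysis plan is deferred. On that view the verb in the hypothesis is merely loose. A proper interaction test would also be too imprecise to settle the matter. Much of this stands: the analysis is exploratory, the primary intention-to-treat ANCOVA is untouched, and power is low. It does not remove the mismatch. Deferral excuses missing detail, but here the document states both a hypothesis and an analysis for the same factors, and the second does not address the first.

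Some stronger readings are tempting but not supported:

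- **The subgroup objective is analysed by this regression and so stays untested.** The Objectives do aim to "identify patient sub-groups for whom AOT is more effective", but Statistical analysis does not assign that aim to this model. It gives no subgroup method, which may sit in the analysis plan.
- **AOT will increase engagement by construction under the third secondary hypothesis.** The measure "engagement in treatment (measured by cumulative number of days in AOT and specialist alcohol treatment") belongs to the exploratory regression. The third hypothesis names no measure.
- **The plan will yield a spurious engagement finding in about half of trials.** One set of invented inputs gives 54% with no adjustment: AOT days 120 + 60 × prognosis, CAU days 20 + 15 × prognosis, outcome 45 + 12 × prognosis with noise SD 30, and my assumed noise SDs for days of 40 and 15. The plan does adjust for known confounders. If covariates carry half of the prognostic variance the share falls to about 20%, and at three quarters to about 9%. With arm also in the model it is 83% unadjusted and 39% at one half. The range is too wide for any single figure to be a consequence of the plan.
- **All three factors are invalid moderators.** Readiness to change has a baseline value and is a legitimate candidate.

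**Conclusion.** The point holds in a limited form. The stated regression does not estimate moderation for any of the three factors. For engagement and 12-month alliance, adding an interaction would not rescue it, because both arise after randomisation and AOT days have no counterpart in CAU. For readiness to change, the baseline value allows a valid test that the document does not specify.

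The logical part needs no assumption beyond the 1:1 design and the document's own timing of measurements. The 6% against 78% contrast rests on an assumed crossover interaction of 0.5 SD per SD, chosen so that the pooled slope is zero. The 39% to 82% range rests on assumed correlations with a wholly unmeasured prognostic factor, so it illustrates residual confounding and is not a forecast. The change should be made, but it concerns a secondary, exploratory question and has no bearing on the primary result.

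**What to change.** In the final analysis plan:

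1. Test moderation by adding an arm × baseline readiness-to-change interaction to the primary ANCOVA. Label it exploratory and report the estimate with its 95% confidence interval.
2. Reword the hypothesis so that readiness to change is the candidate moderator, and engagement and alliance are exploratory process (mechanism) variables.
3. Keep the regression of drinking on engagement and alliance if wanted, but report it as a non-causal association and treat 12-month STAR as descriptive.

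This costs a rewording and one extra model term, with data already collected. The drawback is imprecision: with 128 analysed and a 50/50 binary moderator, the 95% interval for the difference in effect is about ±0.69 SD (1.96 × 0.354). A null result would therefore not rule out moderation, and the report should say so. The article gives the trial status as analysis ongoing. If results by arm have already been seen, the interaction should be reported as added after that.

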### Assertive outreach treatment intervention

Patients in the intervention arm of the study will receive AOT in addition to usual care. AOT will incorporate the following elements [14]:
(i)Each AOT practitioner should have a maximum caseload of 15 AOT patients.(ii)Care provided by a multidisciplinary team (including psychiatrists, community addiction nurses, substance use disorder specialists, community support workers).(iii)Frequent and regular contact between practitioner and patient (at least once a week predominantly in patients’ homes and local community settings).(iv)Assertive engagement – persistent and repeated attempts by the practitioner to make contact, with the emphasis being on maintaining contact and building relationships.(v)Content of sessions will focus on both health and social care needs – including accommodation, leisure, occupation, and physical and mental health, with an emphasis on a patient-led agenda.(vi)Flexibility – practitioners should work flexibly with patients’ goals and include those which are less related to the addiction. The AOT model has abstinence from alcohol as its ultimate clinical goal. However, whilst all treatment aspires to achieve full recovery, it can be an unrealistic short-term goal for more severely dependent drinkers with complex social support needs plus multiple comorbidities, in which case a reduction in harmful drinking will be a more realistic goal.(vii)Openness – practitioners explain their role and aims in care planning and in visits.(viii)Practitioners operate more broadly than in their usual professional roles to provide a wide range of support to patients.(ix)Extended care – AOT will be provided for a period of 1 year during which patients will be introduced to other existing community services who will ultimately provide them with on-going support in the longer-term.

AOT will be used to proactively engage with ARFA patients, to assess their physical and mental health and wider social needs, then to develop shared treatment goals, and to facilitate and coordinate engagement with the relevant care and support to address their multiple presenting needs. The AOT will mainly take place either in the patient’s home or local community settings. A treatment manual has been developed by the research team as part of a previous clinical trial [11].

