### Control intervention

All participants in the control arm of the study will receive CAU i.e. routine clinical practice, so that the hypothesis that CAU + AOT is more effective than CAU alone can be tested. CAU typically involves treatment of presenting physical or mental health problems and referral to specialist addiction services for ongoing help with alcohol related problems. Patients receiving CAU have access to medical detoxification, psychological interventions targeting drinking behaviour and aftercare, which are usually provided by specialist addiction services. But in contrast to AOT, the emphasis will be on the patient’s own motivation to engage with available services. Specialist input from addictions psychiatry, clinical psychology and social work may also be a part of CAU but the assertive and regular nature of contacts in AOT does not feature.

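### The stated engagement variable counts days in AOT, which only one arm can have, so the planned regression of drinking on engagement partly measures allocation

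*Protocol article*

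**What the plan says.** Two secondary hypotheses concern engagement. The third compares the arms: "CAU + AOT will increase engagement with specialist addiction and recovery services compared to CAU alone". The fourth treats engagement as a moderator: "Addiction treatment engagement, readiness to change and therapeutic alliance will moderate treatment effectiveness".

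The article defines engagement once, under Statistical analysis: "engagement in treatment (measured by cumulative number of days in AOT and specialist alcohol treatment". It gives the variable one use, which is to explore its association, together with readiness and alliance, with drinking: "and drinking outcomes using a linear regression adjusted for known confounders". It does not say whether arm is among the confounders, whether the two kinds of days are summed or entered separately, or whether a day in AOT means a day enrolled or a day with contact.

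On exposure to AOT, the intervention section says "AOT will be provided for a period of 1 year", with contact at least weekly. Of control patients, the Control intervention section says "the assertive and regular nature of contacts in AOT does not feature", although they can use specialist addiction services.

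For the remaining secondary outcomes the plan is general: "Secondary analysis will address drinking and other outcomes at 6 and 12 months using appropriate modelling approaches". Service use is collected by AD-SUS interview in both arms at baseline, 6 and 12 months, and AOT contacts are recorded in staff logs (Intervention fidelity).

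**The concern.** A variable that includes time in the randomised treatment is partly the allocation under another name. Two things follow.

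In the regression that the protocol does plan, the arms differ on the explanatory variable because of randomisation. If AOT improves abstinence by any route, patients with more engagement days will drink less, even if attending specialist services makes no difference to anyone. The result would be read as evidence on mechanism, which is one of the trial's objectives, when it only restates the treatment effect. AOT days also cannot serve as a moderator of the arm contrast, since they are zero throughout one arm.

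The definition also does not match the third hypothesis, which is about specialist addiction and recovery services. If it were carried over to that comparison, AOT would start ahead whether or not any patient had been linked to those services.

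A smaller weakness is that time in AOT may reflect the team's effort more than the patient's. The model requires "persistent and repeated attempts by the practitioner to make contact", so a patient who does not respond can remain on the caseload.

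**Working it through.** The protocol gives no figure for engagement, so there is none to reproduce. The definition was checked by reading, and its consequences by two illustrations.

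**Inputs**
- 64 analysed per arm and effect size d = 0.4 (Sample size and power).
- AOT days in controls: 0 (Control intervention).
- AOT days in the intervention arm, D: 365 if enrolled days count (AOT lasts 1 year), or about 52 if contact days count (at least weekly for a year).
- Standard deviation s of specialist treatment days: not given; assumed 20 to 100 days, equal in both arms.

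**A. The stated regression, with arm left out**

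Assume that the components are summed, every AOT patient has D days, specialist days have the same mean in both arms, and engagement is unrelated to drinking within arms. Variables are taken as normal, with no other covariates.

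- Between-arm variance of the engagement variable with equal arms: D²/4. For D = 52 this is 676; for D = 365 it is 33,306.
- Share of its variance that is purely allocation: (D²/4) / (D²/4 + s²).
- Correlation of arm with the outcome: (d/2)/√(1 + d²/4) = 0.2/√1.04 = 0.196.
- Spurious correlation of engagement with the outcome: r = 0.196 × √share.
- Test statistic with 128 patients: t = r√126/√(1 − r²). The chance of p < 0.05 is Φ(t − 1.96) plus the negligible other tail.

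| D | s | share due to arm | r | t | chance of a significant engagement effect |
|---|---|---|---|---|---|
| 52 | 20 | 63% | 0.155 | 1.77 | 42% |
| 52 | 40 | 30% | 0.107 | 1.21 | 23% |
| 52 | 60 | 16% | 0.078 | 0.88 | 14% |
| 52 | 100 | 6% | 0.049 | 0.55 | 9% |
| 365 | 20 | 99% | 0.195 | 2.23 | 61% |
| 365 | 40 | 95% | 0.192 | 2.19 | 59% |
| 365 | 60 | 90% | 0.186 | 2.13 | 57% |
| 365 | 100 | 77% | 0.172 | 1.96 | 50% |

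A simulation of 6,000 trials per row agreed to within about 2 percentage points. With arm added to the model, the rate returned to about 5% in every row.

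**B. If the same variable were used to compare the arms**

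The protocol does not state this use. Suppose specialist days do not differ between arms, and a fraction u of AOT patients accrue D days while the rest accrue none. The mean difference is uD, its standard error is √{[2s² + D²u(1 − u)]/64}, and the chance of a significant result is Φ(uD/SE − 1.96). For example, with u = 1, D = 52 and s = 100, SE = √(20,000/64) = 17.68, 52/17.68 = 2.94, and Φ(0.98) = 84%.

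| uptake u | D | s = 20 | s = 40 | s = 60 | s = 100 |
|---|---|---|---|---|---|
| 1 | 52 | >99.9% | >99.9% | 99.8% | 84% |
| 0.5 | 52 | about 100% | 92% | 65% | 30% |
| 0.25 | 52 | 82% | 40% | 22% | 11% |
| 0.25 | 365 | 99.5% | 99% | 98% | 93% |

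With D = 365 and uptake of a half or more, every entry rounds to 100%. On specialist contact alone, the rate under no true difference is the nominal 5%.

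**The case against.** The strongest reply is that the variable is used only as an explanatory variable in an exploratory analysis. Engagement, readiness and alliance are the same three factors as in the fourth hypothesis, not the third, and AOT is an addiction treatment, so counting time in it as treatment exposure is natural. The protocol's own wording keeps AOT and specialist services apart, and the choice of confounders can be settled in the final analysis plan, which the article says will follow.

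Much of this stands, and it limits what can be said. A reader might infer that the third hypothesis would be confirmed by allocation alone. The documents do not support that: nowhere is this variable named as the test of that hypothesis, and part B shows that even if it were, a significant result would not be assured when uptake is low and only contact days count (11% to 82% at quarter uptake). Nor is it the only engagement measure available. It is the only stated definition, but the AD-SUS records service use in both arms and the Abstract lists other health service use as a secondary outcome.

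A reader might also compare a full enrolled year in AOT with a control patient's course of specialist treatment. With an assumed 12-week course the ratio is 365/84 = 4.3, but with weekly contact days it reverses to 52/84 = 0.6. The documents fix neither the course length nor the unit, so that ratio is no measure of the problem.

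What the reply does not remove is the flaw in the stated use. The article does not leave engagement undefined. It fixes a definition with a component that only one arm can have, and mentions no adjustment for arm. Calling the analysis exploratory does not make its coefficient interpretable.

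**Conclusion.** The concern holds for the regression that the protocol describes. The engagement variable is partly a proxy for allocation, and unless arm is in the model, an effect of AOT on drinking will be attributed to engagement. Under the assumptions of part A, between 6% and 99% of the variable's variance is allocation, and a spurious engagement effect appears in 9% to 61% of trials against a nominal 5%. The range depends mainly on whether contact or enrolled days are counted. If AOT has no effect on drinking, this distortion does not arise.

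For the third hypothesis the point is conditional: the protocol names no variable for that comparison, but this one would favour AOT by construction. The primary outcome is untouched. This should be corrected, but it affects only secondary and exploratory conclusions.

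**What to change.** In the final analysis plan:

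1. Define engagement as contact with specialist addiction and recovery services other than the AOT team, counted the same way in both arms from the AD-SUS at 6 and 12 months.
2. Use that measure for the between-arm test of the third hypothesis.
3. Use it also in the pooled regression of drinking outcomes, with treatment arm in the model.
4. Analyse AOT exposure separately, within the AOT arm only, as contacts actually made according to the staff contact logs.

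No new data collection is planned for this, since both sources are already part of the trial. The AD-SUS items are not shown, so it should be checked that contacts with the AOT team can be told apart from other addiction services. The article reports that analysis is ongoing; if the regression has already been run on the combined variable, the revised version should be labelled as a later change and shown beside it. The cost is a little more analysis work and possibly a less favourable engagement result for AOT.
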